##### Cardiorespiratory and symptom responses

During weeks 1, 4 and 8 of the training period, participants in the experimental group will be asked to complete one of two or three (week 3 onwards) HIIT sessions in the same laboratory used to conduct the ramp-based cycle ergometry test. During these sessions, measurements will be collected of minute ventilation, breathing pattern, VO_2_ and VCO_2_, HR, SpO_2_ and BP. Breathlessness and muscle fatigue will be assessed using the modified Borg scale [42].

##### Behaviour change techniques

The HIIT sessions will be audio recorded over the course of the 8-week program. The purpose of this will be to allow for qualitative analysis and reporting of BCTs [60], as recommended by the CONSORT guidelines [61]. Behaviour change techniques are defined as the active component of an intervention that targets a specific behaviour. These techniques can be used alone, or in combination with another technique. Of note, to be considered a BCT, the intervention needs to be observable, able to be replicated, and designed to alter existing or stimulate new behaviour [60]. Some examples of BCTs are reinforcement, self-monitoring, feedback, problem solving, graded tasks and reward. The BCTs will be reported in accordance with the Taxonomy (v1) by Michie et al. [60]. All HIIT sessions will be audio recorded, unless the participant ‘opts-out’. This audio recording process will also allow for fidelity checking of the sessions if required by the relevant ethics committee.

#### Control group

Participants allocated to the control group will be contacted once a week by a physiotherapist to discuss changes to their symptoms, healthcare utilisation and participation in exercise over the preceding week. Participants will be allowed to choose the way in which this contact is made; phone calls, texts or emails. If a participant allocated to the control group reports any symptoms that are suggestive of an exacerbation, they will be referred to the CF team for medical review.

### Statistical analyses

The results of this study will be analysed according to the intention-to-treat principle using Statistical Package for the Social Sciences (SPSS) (Version 22, SPSS, Chicago, IL, USA). The distribution of data will be checked using frequency histograms. A *p* value of < 0.05 will be considered statistically significant. Audio recording of the HIIT sessions will be analysed using NVivo software.

To address differences between the experimental and control group, between-group differences in all outcomes (e.g. T_lim_, VO_2peak_, HRQoL, exercise self-efficacy, feelings of anxiety, depression and enjoyment) will be assessed using linear mixed models. Baseline measures will be used as a covariate and group allocations will be used as a fixed factor. Total in work done (i.e. training dose) will be considered in the analyses by entering this parameter as a random factor in the mixed effects model. To address the proportion of participants who develop post-exercise muscle soreness, the severity of post-exercise muscle soreness in those who develop it over the 8 week intervention period and tolerance of the HIIT program, descriptive statistics, such as frequency, mean and standard deviation (SD) or median and interquartile range will be used. To explore differences in measures of cardiorespiratory and symptom responses throughout the HIIT program, an analysis of variance (parametric) or a Friedman’s test (non-parametric data) will be used.

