### Randomisation and allocation concealment

Participants will be randomly allocated, on a 1:1 ratio, to either the experimental or control group. Concealment of the allocation sequence will be ensured by using a central randomisation service (the National Health and Medical Research Council randomisation service). A minimisation algorithm will be used to stratify for site of recruitment (i.e. SCGH or PCH), spirometry (i.e. mild [FEV_1_ ≥ 70% predicted], moderate [FEV_1_ 40 to 69% predicted] or severe [FEV_1_ ≤ 39% predicted]) and the use (or not) of Ivacaftor, which is a medication that improves lung function, weight, HRQoL and reduces the rate of exacerbation [40].

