### Sample size calculations

Constant power tests have been widely used to demonstrate increases in exercise capacity following a period of exercise training (i.e. pulmonary rehabilitation) [43, 47], are also more likely to reflect performance of activities of daily living [62], as they are performed at a moderate intensity, compared to tests of peak exercise capacity [22, 43] and when conducted at 80% of the W_max_ are demonstrated to be highly repeatable in people with CF [63]. For these reasons, the sample size calculation for this study has been based on the measurements of T_lim_ during a constant work rate test, conducted at 80% of W_max_ [43]. There is limited information pertaining to the minimal clinically important difference (MCID) for the T_lim_ in people with CF. However, in people with COPD, the MCID for T_lim_ during a constant work rate test has been proposed to be 100 s [43]. In order to detect a between-group difference of 100 s (MCID for T_lim_ in COPD), with a SD of 99 s (largest of the 2 SDs reported for T_lim_ in a CF population that will be similar to that recruited in the study described in this proposal [48]) (α = 0.05 and 1-β = 0.8) a sample size of 16 per group (*n* = 32 in total) is required. This sample size has been inflated by 20% to account for possible loss to follow-up. Therefore, the recruitment target for this study will be 40.

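### The outcome model omits the three minimisation factors, so if they are prognostic beyond the baseline value the test is conservative and some power is lost

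*Protocol article*

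**What the plan says.** Under Randomisation and allocation concealment, the protocol article states: "A minimisation algorithm will be used to stratify for site of recruitment (i.e. SCGH or PCH), spirometry". Spirometry enters in three classes (mild, moderate, severe). The third factor is "the use (or not) of Ivacaftor, which is a medication that improves lung function, weight, HRQoL and reduces the rate of exacerbation".

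Under Statistical analyses, all outcomes, from T_lim to enjoyment, are to be compared between groups with linear mixed models. The terms are listed: "Baseline measures will be used as a covariate and group allocations will be used as a fixed factor". Total work done, described as the training dose, "will be considered in the analyses by entering this parameter as a random factor in the mixed effects model". Site, FEV1 class and ivacaftor use do not appear.

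Under Sample size calculations, the trial is sized "In order to detect a between-group difference of 100 s", "with a SD of 99 s (largest of the 2 SDs reported for T_lim_ in a CF population" and the remaining inputs "α = 0.05 and 1-β = 0.8) a sample size of 16 per group". Inflation for 20% loss gives a target of 40. The SD takes no credit for baseline or factor adjustment.

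**The concern.** Minimisation makes the arms more alike on the chosen factors than simple randomisation would. If those factors predict the outcome, the true sampling variance of the treatment difference falls. A model without them still counts their variation as error that could differ by chance between arms. Its standard error then exceeds the real sampling error, the test rejects too seldom under the null, and the confidence interval is too wide. The design buys precision that the analysis does not use.

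The article gives some reason to expect prognostic value. Its rationale for ivacaftor names an effect on HRQoL, which is an outcome analysed with this same model. The Background names reduced lung function among the causes of reduced exercise capacity in CF. With 32 planned completers there is little precision to spare.

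**Working it through.** **1. The plan's own figure.** Inputs from Sample size calculations: difference 100 s, SD 99 s, α = 0.05 (two-sided assumed; one-sided would give 13 per group), power 0.80.

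n per group = 2 × (1.960 + 0.842)² × 99² / 100² = 15.4, rounded up to 16. Total 32; 32 / 0.8 = 40. The stated size reproduces. At 16 per group, power is 81.5% by the normal approximation and 79.0% by the noncentral t.

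**2. Degrees of freedom.** Site takes 1, FEV1 in three classes 2 and ivacaftor 1, so 4 in all, or 3 with FEV1 as a continuous term.

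**3. The unknown quantity.** Let R² be the share of outcome variance, after adjustment for baseline, that the three factors explain. The documents give no value, so it is an assumption and a range is shown.

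**4. Simulation with a residual SD of 99 s given baseline.** Assumptions: minimisation with a biased coin of 0.8; 20% at the children's site; FEV1 classes 50/35/15%; 10% on ivacaftor; 6,000 runs per cell. Analysis of covariance with baseline and group was compared with the same model plus the factors (4 df). Training dose was not simulated. As a check, the simple SE is 99 × √(2/16) = 35.0 s, close to the simulated 35.6 to 35.8 s.

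Results with 32 analysed (SEs and type I error under no effect; power at 100 s):

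| R² | Model SE, factors omitted | True sampling SD | Type I, omitted | Type I, included | Power, omitted | Power, included | Change |
|---|---|---|---|---|---|---|---|
| 0 | 35.6 s | 36.0 s | 5.3% | 5.0% | 78.1% | 74.8% | −3.3 |
| 0.1 | 35.7 s | 34.4 s | 4.4% | 4.9% | 76.9% | 77.4% | +0.5 |
| 0.2 | 35.7 s | 33.5 s | 3.6% | 4.9% | 79.4% | 84.1% | +4.7 |
| 0.3 | 35.8 s | 32.2 s | 3.2% | 4.8% | 79.7% | 87.2% | +7.5 |

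Monte Carlo error is about 0.3 points for type I error and 0.5 points for power. With all 40 analysed, power goes from 87.0% to 84.8% at R² = 0, 87.4% to 88.4% at 0.1, 88.0% to 91.8% at 0.2, and 89.1% to 95.1% at 0.3.

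**5. Simulation giving credit for baseline adjustment.** Assume a baseline to follow-up correlation of 0.5 (not in the documents). The residual SD is 99 × √(1 − 0.25) = 85.7 s and the simple SE is 85.7 × √(2/16) = 30.3 s. With 32 analysed and R² of 0.2 to 0.3, the model SE with factors omitted is about 30.8 s against a true 29 s, and type I error is about 3.5%. Unadjusted power at 100 s is about 88%, and adjustment adds about 3 to 6 points. At R² = 0 adjustment costs 3 to 4 points; break-even is again near R² = 0.1. The gain is smaller than in step 4 because power starts nearer its ceiling.

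**The case against.** **Scope.** This is a condensed article without its SAP, and full covariate lists are often left to the SAP. That would dispose of the point if the article were silent. It is not: it names a covariate, a fixed factor and a random factor for every outcome, and a reader following it would fit that model. Baseline measures might be meant to include FEV1, but the phrase directly follows the list of outcomes and most naturally means each outcome's own baseline value.

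**The loss is not shown to occur.** A reader might infer that the standard errors are certainly too wide and power certainly lost. The documents do not support that. What matters is what the factors explain beyond baseline, and no figure is given. Under Assessment day two, T_lim is measured at 80% of each participant's own W_max, and the load is raised at baseline for anyone not symptom-limited at 10 min; this may weaken any link with FEV1. Only ivacaftor is given a rationale, which does not mention exercise capacity, and nothing says that site is prognostic. This objection stands, and makes the point conditional.

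**The design target survives.** A reader might also infer an underpowered trial or unsound positive results. Neither follows. With the factors omitted, power at 100 s stays at about 77% to 80% with 32 analysed even when baseline adjustment earns no credit, and at about 88% when the assumed correlation of 0.5 is credited. The error is conservative.

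**The model is not baseline and group alone.** Training dose is also entered. It arises after randomisation and does not stand in for the minimisation factors, but it was not simulated, so the figures describe the model without it.

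**Conclusion.** The mismatch between the allocation method and the stated model is real; its consequence is conditional. If the factors explain 20% to 30% of residual variance, the model-based SE is too wide, type I error is about 3.5%, and the power loss at 100 s with 32 analysed is about 3 to 6 points (4.7 to 7.5 if baseline adjustment is given no credit). At about 10% there is little to choose; at zero, omission is slightly better. These figures rest on assumed prevalences, an assumed biased coin and an R² that the documents do not give. The sample size stands and false positives are not inflated. This is an inexpensive gain in efficiency and calibration, not a flaw that threatens the trial's conclusion.

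**What to change.** State that the model for each outcome includes, as fixed covariates alongside the baseline value and group, site of recruitment, FEV1 % predicted as a continuous term and ivacaftor use. Add a rule, fixed before the data are seen, for collapsing or dropping a factor with too few participants at one level; under the prevalences assumed above, 10% of 32 is only about 3 ivacaftor users. If the SAP already does this, bring the article's description into line with it.

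The change takes a sentence or two and uses variables already collected for randomisation. It also removes any later choice between adjusted and unadjusted results. The costs are 3 to 4 degrees of freedom, about 3 to 4 power points if the factors prove not to be prognostic, and a linearity assumption for FEV1.

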#### Experimental group

Participants allocated to the experimental group will be asked to complete an 8-week cycling-based HIIT program. Each training session will involve a 2-min active ‘warm up’ at 15 to 20 W, followed by a 30-s ‘work’ phase and 30-s ‘rest’ period, repeated six times. The work to rest periods will be followed by a 2-min active ‘cool down’ period at 15 to 20 W. Therefore, the total training time per session, inclusive of rest periods, will be 10 min. Each session will be supervised by a physiotherapist who is trained in the management of people with CF. To minimise the onset of post-exercise muscle soreness and optimise adherence, the training program will commence with a ‘lead in’ phase which will involve only two sessions of HIIT in weeks 1 and 2. Thereafter, between weeks 3 and 8, HIIT will be undertaken three times a week (i.e. total 22 sessions over 8 weeks). The training intensity will be prescribed using measurements of maximum work rate (W_max_) achieved during the ramp-based cycle ergometry test completed during the baseline assessments. Specifically, the first training session will be prescribed at 60% of W_max_, with the goal of achieving a training intensity equal to 80% of W_max_ during the fourth training session (i.e. the end of week 2). Thereafter, training intensity will be increased as rapidly as symptoms of breathlessness and muscle fatigue permit. Training will be completed at one of two sites, with the participant permitted to choose the site that is most convenient for them. The model of exercise bike used for the HIIT sessions will be identical across all training sites (Orbit Eco Generator Interval Bike OEB2002, Perth, Australia). Only a single participant will be permitted to use the exercise room on any day, with stringent hand hygiene and cleaning procedures adhered to at all times to reduce the risk of cross contamination between participants [54]. The intervention will be conducted and reported in accordance with the TIDieR checklist [55] and CERT guidelines [56, 57].

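### Training dose, which arises after randomisation and only in the HIIT arm, is a random factor in the primary between-group model: the estimate stays unbiased, but precision and power can be lost

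*Protocol article*

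**What the plan says.** The Statistical analyses section of the protocol article commits to intention to treat: "The results of this study will be analysed according to the intention-to-treat principle". It then gives one linear mixed model, introduced by "To address differences between the experimental and control group, between-group differences in all outcomes"; T_lim, the primary outcome, is among the outcomes listed. The fixed part is clear: "Baseline measures will be used as a covariate and group allocations will be used as a fixed factor". The next sentence says of total work done: "i.e. training dose) will be considered in the analyses by entering this parameter as a random factor in the mixed effects model". Nothing there or elsewhere marks that term as secondary, exploratory or confined to one arm, and it is the only random term named.

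The sections on the two groups show where dose comes from. In the Experimental group section, "Participants allocated to the experimental group will be asked to complete an 8-week cycling-based HIIT program", and after the lead-in "training intensity will be increased as rapidly as symptoms of breathlessness and muscle fatigue permit". In the Control group section, "Participants allocated to the control group will be contacted once a week by a physiotherapist"; no training session and no measurement of work is described for controls.

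**The concern.** Total work done follows from being allocated to HIIT and from how well the participant tolerates it. It is not a baseline characteristic, and it is all but determined by arm: some positive amount in one, nothing or undefined in the other. A term of this kind does not belong in a model meant to deliver the randomised comparison.

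The primary test of T_lim and every secondary between-group comparison use this model. The sample size of 16 completers per arm makes no allowance for the extra term, so any loss of precision falls on a small trial with little power to spare.

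**Working it through.** **Inputs.** From Sample size calculations: difference 100 s, SD 99 s, α = 0.05 (two-sided assumed), power 0.80, 16 per group, 20% inflation, target 40. Assumed here: control dose is 0 for everyone and HIIT doses are all different.

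**1. The plan's own figure.** n per arm = 2 × (1.96 + 0.84)² × (99/100)² ≈ 15.4, rounded up to 16; 32/0.8 = 40. Both figures reproduce. The standard error (SE) behind them is 99 × √(2/16) = 35.0 s, and power is Φ(100/35.0 − 1.96) = 0.815. (With the t distribution, n is 16.4 and power at 16 is 0.789, a difference that does not matter here.) The sample size therefore matches a model without the dose term.

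**2. What the random factor does.** All 16 controls share one level; each HIIT participant is the only member of a level. Let σ²u be the dose variance component and σ²e the residual variance. Then

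Var(group difference) = (σ²u + σ²e)/16 + σ²u + σ²e/16.

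The middle term is the controls' shared intercept. It is not divided by 16, because the whole arm has a single draw. With σ²u + σ²e = 99² = 9801:

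- σ²u 10% of the total: √(612.6 + 980.1 + 551.3) = 46.3 s, power 0.58
- 25%: √(612.6 + 2450.3 + 459.4) = 59.3 s, power 0.39
- 50%: √(612.6 + 4900.5 + 306.3) = 76.3 s, power 0.26

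The data identify σ²u only through the excess of HIIT-arm over control-arm variance. When the true variances are equal, that excess is negative in about half of samples. The component is then estimated as zero and the SE is not inflated.

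**3. Simulation by restricted maximum likelihood** (600 runs, no baseline covariate, test on 30 degrees of freedom):

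| Model | Mean estimate | Mean SE | Power | Rejection when no effect |
|---|---|---|---|---|
| Group only | 101.0 s | 34.4 s | 0.81 | 0.052 |
| Group + random dose factor | 101.0 s | 52.1 s (median 42.0) | 0.54 | 0.027 |

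The variance component was zero in 47% of the runs with a true 100 s difference. With baseline as covariate and an assumed baseline-to-follow-up slope of 0.5 (2000 runs), power was 0.89 without the term and 0.60 with it.

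**4. If HIIT outcomes vary more.** Take an assumed HIIT-arm SD of 120 s, slope 0.5 and baseline SD 99 s. Baseline explains 0.25 × 9801 = 2450. The remaining variances are 7351 (control) and 14400 − 2450 = 11950 (HIIT), an excess of 4599. Without the term, SE = √((7351 + 11950)/16) = 34.7 s. With it, SE = √(11950/16 + 4599 + 7351/16) = 76.2 s, so power ≈ Φ(100/76.2 − 1.96) = 0.26. Simulation gave 0.78 without the term and 0.27 with it.

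**5. Other readings of the sentence.**

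- *Dose as a covariate.* The group coefficient becomes the effect of HIIT at zero dose. With 1:1 allocation and coefficient of variation CV in the HIIT arm, the variance inflation factor is 1 + 0.5/CV². At an assumed CV of 20% this is 13.5 (SE 3.7 times larger); at 30% it is 6.6 (SE 2.6 times larger). With an assumed dose-response of 100 s per mean dose and CV 25%, the simulated group estimate fell from about 100 s to between 0 and 5 s.
- *Dose as a random coefficient.* Under the same dose-response and CV, the estimate fell from 98.7 to 41.1 s. With no dose-response it did not shrink (105.0 against 100.0 s).
- *Control dose missing.* Listwise deletion removes the control arm and there is no contrast to estimate.

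**The case against.** The strongest defence is that the protocol says random factor. A zero-mean random factor beside a fixed group term does not move the group estimate, and the test errs on the conservative side, so no false-positive risk arises. That stands. A reader might infer that the dose term absorbs the treatment effect, or that the model as worded no longer targets the intention-to-treat difference. The documents do not support either: both need dose fitted as a covariate or random coefficient, with outcome depending on dose, and the protocol does not specify that.

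A reader might also infer that most of the power is lost. At the only SD in the document, 99 s, the loss is about one third (0.81 to 0.54, or 0.89 to 0.60). Larger losses need a HIIT-arm SD that appears nowhere in the protocol.

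The zero coding for controls is likewise an inference. The weekly contact asks controls about exercise participation, so some dose might be constructed for them, but no measurement of work is described.

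The sentence may have been meant as a dose-response analysis. If so, the text does not say it: the term is placed in the model that yields the between-group differences, and the gloss as training dose excludes work done during the exercise test.

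**Conclusion.** The plan is wrong as written, and the defect is one of precision rather than bias. The literal model leaves the group estimate unbiased, but its SE can be inflated because one random intercept shared by all controls is confounded with the group contrast. At the protocol's inputs, mean SE rises by about half and power drops to roughly 0.54 to 0.60. Whether the penalty applies in a given dataset depends on a poorly determined variance component.

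These figures rest on control dose being zero, distinct HIIT doses, 16 completers per arm and, for the adjusted figures, a slope of 0.5. The alternative readings give no better comparison: they change the meaning of the group coefficient or remove the control arm. No reading gives the analysis for which the trial was sized.

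**What to change.** Delete the training-dose term from the between-group model. The primary analysis then regresses follow-up outcome on group and baseline value, with participants analysed as randomised; the secondary between-group outcomes follow the same form. If dose-response is of interest, report it separately, within the HIIT arm only, labelled exploratory and non-randomised.

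The cost is a change of wording, best made before follow-up data are analysed. No data collection, recruitment target or trial procedure changes, and the stated sample size then corresponds to the comparison it was calculated for.

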### Assessment period

Both prior to randomisation (i.e.baseline) and following the intervention period (i.e. follow-up), participants will complete assessments over two non-consecutive days; assessment day one and assessment day two. Each assessment visit will last 1.5 h, and both visits will be completed within 2 weeks. During both the baseline and follow-up assessments, descriptive variables will be recorded related to age, gender, height, weight, genotype and spirometry (Medgraphics USB Spirometer, MCG Diagnostics, Minnesota, USA). Measures related to the primary aim will be collected in both groups during the baseline and follow-up assessment. This will comprise exercise capacity, HRQoL, exercise self-efficacy, feelings of anxiety, depression and enjoyment. The follow-up assessments of these outcomes will be completed by an assessor who is blinded to group allocation. Measures related to the secondary aim will be collected in the experimental group only and will comprise post-exercise muscle soreness (measured weekly), tolerance (measured at every HIIT session) and cardiorespiratory and symptom responses to HIIT (measured at week 1, week 4 and week 8 of the HIIT program) will be measured throughout the 8-week period. Details of these measurements are provided below.

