If a participant in the experimental group reports the onset of symptoms indicative of an exacerbation of CF (i.e. increased sputum volume, changes in the characteristics of sputum, blood present in the sputum, increased cough, pain from coughing, new wheeze or increased wheeze, new or increased chest tightness, shortness of breath or difficulty breathing, increased fatigue or lethargy, fever, loss of appetite or weight, sinus pain or tenderness) [58], they will be referred to their respective CF team for medical review. If an exacerbation is diagnosed by the treating CF team, the participant will be invited to continue participating in HIIT sessions once deemed to be medically stable by a CF clinician. Medical stability has been defined as being afebrile, having resting BP, HR and SpO_2_ within limits of the participants’ baseline values and/or deemed stable by the treating CF clinician. In the event of missed attendance to HIIT sessions, the training program will be extended by a maximum of 2 weeks so that the participant will have 10 weeks to complete the 22 HIIT sessions.

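### ANOVA or Friedman's test on the week 1, 4 and 8 responses wastes or mishandles incomplete repeated data; a mixed model, with delivered work rate shown beside each week, would serve better

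*Protocol article*

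**What the plan says.** All references are to the protocol article. Under Assessment period, the measures taken in the experimental group only include "cardiorespiratory and symptom responses to HIIT (measured at week 1, week 4 and week 8 of the HIIT program"). The section on cardiorespiratory and symptom responses places these measurements in the laboratory: "During weeks 1, 4 and 8 of the training period, participants in the experimental group will be asked to complete one of two or three" HIIT sessions there. Each person therefore contributes at most three measured sessions.

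For comparing them, Statistical analyses states: "To explore differences in measures of cardiorespiratory and symptom responses throughout the HIIT program, an analysis of variance (parametric"), with Friedman's test as the non-parametric alternative. It does not say whether the ANOVA is a repeated-measures one. The same section uses linear mixed models for the between-group outcomes.

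Under Experimental group, "the first training session will be prescribed at 60% of W_max_, with the goal of achieving a training intensity equal to 80% of W_max" by the fourth session, at the end of week 2. After that, "training intensity will be increased as rapidly as symptoms of breathlessness and muscle fatigue permit". The same section foresees absences: "In the event of missed attendance to HIIT sessions, the training program will be extended by a maximum of 2 weeks".

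**The concern.** Two features of the data fit the named tests poorly.

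First, the data are repeated and may be incomplete. Friedman's test and the usual repeated-measures ANOVA need a full row, so a person who misses the week 8 laboratory session also loses the week 1 and week 4 data. An ordinary one-way ANOVA would keep every session but treat three sessions from one person as if they came from three people. Each reading of the sentence has a fault.

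Second, the work rate is meant to rise between the measured weeks. Oxygen uptake, heart rate, ventilation and Borg scores all depend on work rate. A difference between weeks, or its absence, therefore mixes the load with any adaptation to training. A reader shown only the responses and a p-value cannot tell these apart.

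At stake are some precision in a small group and the clarity of secondary aim (iii), which is to report these responses over the program.

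**Working it through.** **Group size.** The protocol gives no figure for this analysis, so the group size comes from its sample size section. With a difference of 100 s, SD 99 s, α = 0.05 (taken as two-sided) and power 0.80, the normal approximation gives 2 × (1.960 + 0.842)² × (99/100)² = 15.4, so 16 per group and 32 in total. Then 32/(1 − 0.20) = 40. This reproduces the plan. Allocation at 1:1 gives about 20 in the training group, of whom 20 × 0.8 = 16 would remain after the planned loss.

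**Complete cases.** Assume that each measured session is missed independently with probability m. The expected number with all three is 20 × (1 − m)³:
- m = 5%: 17.1
- m = 10%: 14.6
- m = 20%: 10.2

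The expected number with at least one session, all of whom a mixed model can use, is 20 × (1 − m³). This is 19.8 or more in each case.

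**Precision of the week 8 minus week 1 contrast.** Set the total variance to 1 and assume an intraclass correlation ρ = 0.6, equal for every pair of weeks. With n complete cases the variance is 2(1 − ρ)/n.

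*Losses are dropout at the planned 20%: 16 complete, 4 lost.*
- Complete cases: 0.8/16 = 0.0500.
- Mixed model, all four lost after week 1: (1 − ρ²)/16 + (1 − ρ)²/20 = 0.64/16 + 0.16/20 = 0.0480. The ratio is 0.96.
- Mixed model, all four lost after week 4: the regression of week 8 on weeks 1 and 4 has coefficients ρ/(1 + ρ) = 0.375 each and residual variance 1 − 2ρ²/(1 + ρ) = 0.55. The variance is 0.55/16 + (0.375² + 0.625² − 2 × 0.375 × 0.625 × 0.6)/20 = 0.0344 + 0.0125 = 0.0469. The ratio is 0.94.
- The cut is therefore 4% to 6%, about 5%.

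*Sessions are missed independently.* Generalised least squares over the possible patterns, with variance components taken as known, gives:
- m = 10%: at the expected pattern counts, 0.0463 against 0.0549, a ratio of 0.84 and a cut of about 16%. Averaging over simulated patterns gives 0.83.
- m = 20%: averaging over simulated patterns gives a ratio of 0.67, a cut of about 33%. The expected pattern counts give 0.70.

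For ρ between 0.4 and 0.8 the averaged ratios at 10% and 20% stay within 0.82 to 0.84 and 0.66 to 0.69.

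**Work rate.** If the week 1 laboratory session is the first session and the 80% goal is met, the prescribed rise is 80/60 = 1.33, or one third. If it is the second session, on an assumed straight-line lead-in (60, 66.7, 73.3, 80), the rise to 80% is 80/66.7 = 1.20, or one fifth. The article does not say which session is measured, 80% is a goal, and the increase after week 2 has no stated size. The documents therefore fix the intended direction of the change but not its amount.

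**The case against.** The strongest defence is that the aim is only to report the responses elicited in the sessions, and that the analysis is described as exploratory. For responses at the intensity actually delivered, an unadjusted comparison targets the right quantity. Tolerance is a separate aim with its own descriptive measures. Nowhere does the article say that a week effect will be read as adaptation. This stands.

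A reader might infer that the tests are invalid because week is confounded with intensity. With assumed work rates of 65%, 90% and 100% of W_max and an assumed response slope, a simulation does make ANOVA and Friedman's test significant in every run when the response at a given work rate has not changed. But that is a null hypothesis the protocol never poses. Nor would adjusting for work rate settle the matter. After week 2 the work rate is paced by breathlessness and muscle fatigue, which are among the responses analysed, so adjustment changes the question and conditions on something those responses drive.

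A reader might also infer that anyone who misses a session is dropped. Only the three measured laboratory sessions matter, not all 22, and a plain ANOVA would drop nobody. The laboratory visit can be any of two or three sessions in its week, and the program can be extended by up to 2 weeks; both should reduce losses. Independent missingness of 20% leaves 49% of people incomplete, which is pessimistic beside the planned 20% loss.

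Finally, pairing ANOVA with Friedman's test suggests that a within-person ANOVA is meant, and a condensed article may leave the detail to the full plan. That narrows the fault to the complete-case one but does not remove it, because the tests themselves are named.

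**Conclusion.** The point holds as a minor improvement. The named tests either discard people with incomplete measured sessions or ignore the pairing, and a better method is already in use in the same section. The gain is small to moderate and depends on the pattern of missing sessions: about 5% of the contrast's variance under 20% dropout, and about 16% (33%) under independent missingness of 10% (20%) per session. These figures assume 20 participants and an intraclass correlation of 0.6; the documents give neither a missing-session rate nor a correlation.

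On intensity, the documents support a reporting point only. Week differences will reflect the work rate as well as adaptation, and the reader should be shown both. They do not support the claim that the unadjusted comparison is wrong, nor a fixed figure for the rise in load. The primary outcome and the sample size are untouched.

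**What to change.** Replace the sentence on ANOVA or Friedman's test with a linear mixed model for each response: week (1, 4, 8) as a fixed factor, a random participant intercept, and all available laboratory sessions. Keep Friedman's test as a sensitivity check for the ordinal Borg scores.

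Report the delivered work rate (% W_max) beside each week's response, and state that differences between weeks reflect intensity as well as adaptation. Do not make a work-rate-adjusted model the main analysis; label any adjusted contrast as descriptive.

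The cost is a change of wording and one extra row in a table; no new visits or measures are needed beyond noting the work rate at each measured session. The downsides are that the model assumes approximate normality, which is questionable for Borg scores, and that a random intercept assumes the same correlation between any two weeks.
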